### Data analysis

All quantitative data will be double-entered by an experienced, independent data entry company with whom the MRC Epidemiology Unit has an established agreement. Statistical analysis will be performed using STATA™ statistical software. All qualitative data will be transcribed verbatim and analysed using Microsoft Excel™ or the Framework™ software.

Important baseline characteristics of participants in the two groups will be described. The main analyses will compare the intervention and control groups by ‘intention-to-treat’. A secondary ‘per protocol’ analysis will be undertaken among those completing the intervention programme based on attendance at 4/5 sessions (80 % attendance). Comparisons will adjust for age, sex, birth weight, age when formula-milk was started, and other potential confounding variables. Since effects may differ between babies who are fully formula-fed and those who are mixed fed (breast and bottle), provided there are sufficient babies in the two groups, sub-group analysis for the primary outcome will be calculated within each of the two feeding practice subgroups. In addition to the primary outcome of change in weight SDS from birth to 12 months, there are a number of secondary outcomes.

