The intervention will be delivered by trained facilitators (research nurses) from the baby’s enrolment in the trial (2 to 14 weeks old) to 6 months and will consist of three face-to-face sessions and two telephone contacts in addition to two leaflets based on SCT (Fig. 1). The face-to-face sessions will last approximately 30 to 45 min and the telephone contacts 15 to 20 min. Since social support is important, both parents will be encouraged to attend the face-to-face sessions. During the first session, the facilitator will talk parents through the ‘healthy infant growth and nutrition’ leaflet that explains the new feeding recommendations (Table 2) and the growth charts. The leaflet does not just impart knowledge about amounts of formula-feeds, hunger cues, growth charts and rapid weight gain, but also aims to encourage recommended feeding behaviours by strengthening self-efficacy and perceived benefits about following the recommendations. Demonstration of correct feed preparation (if required) and explanation of the feeding recommendations will be provided. Parents will be encouraged to make a feeding plan and provided with stickers to put on the formula milk packets. When the baby is 4-months old, parents will be invited for a second session and advice on weaning and feedback on baby’s growth will be provided. Two phone-calls - when the baby is age 2 to 3 months and 5 months - will be made to monitor progress with following recommendations and to support the parents with ongoing goal setting, action planning, self-monitoring and problem-solving. At the 6-month visit, the baby’s growth will be plotted on the WHO growth charts. Facilitators will feed back this information to parents, and they will be encouraged to monitor the growth of their babies also after the end of the intervention delivery at 6 months. Growth monitoring is important because parents are not very good at identifying obesity in their children [36], so any programme to prevent obesity must include early identification.

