### Control group

The control group will be offered the same number of contacts with facilitators (attention control) and general information about formula-feeding (bottles, teats, sterilisation, making up feeds) will be discussed. The 4 to 6 weekly phone calls will be used to discuss general issues (parenting, sleep, etcetera), to monitor feed quantity and frequency and to encourage continued participation in the study.

Parents in both groups will be given a help-line number to contact the study team about feeding issues.

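### The secondary per-protocol analysis selects on attendance after randomisation and, as worded, in the intervention arm only; apply the rule to both arms, label the result non-randomised, and add a complier-average estimate with its assumption stated

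*Protocol article*

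**What the plan says.** All references are to the protocol article.

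- **Data analysis.** The main comparison is by allocated group: "The main analyses will compare the intervention and control groups by ‘intention-to-treat". The per-protocol analysis is called secondary; its set is fixed by this rule: "analysis will be undertaken among those completing the intervention programme based on attendance at 4/5 sessions (80 % attendance"). The text does not say whether the rule also applies to controls. On adjustment: "Comparisons will adjust for age, sex, birth weight, age when formula-milk was started, and other potential confounding variables".
- **Intervention group.** The programme "will consist of three face-to-face sessions and two telephone contacts", five contacts in all, running from "enrolment in the trial (2 to 14 weeks old) to 6 months". The calls are placed "when the baby is age 2 to 3 months and 5 months". The first session covers the leaflet, the new feeding recommendations and a feeding plan. The second, at 4 months, includes feedback on the baby's growth.
- **Control group.** "The control group will be offered the same number of contacts with facilitators", with different content.
- **Table 1.** At 4 months, baby weight and length are scheduled for the intervention group only.
- **Recruitment and retention.** Families who drop out of the intervention are still to be encouraged to come for outcome measurement.

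**The concern.** Membership of the per-protocol set depends on what families do after allocation. Parents who keep four of five appointments may differ from those who do not in ways related to infant growth, so randomisation no longer protects the comparison. As worded, the restriction refers to a programme that only one arm receives. Read that way, selected intervention families are compared with unselected controls.

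The selection need not be only social. Intervention parents get growth feedback at 4 months, and the 5-month call and 6-month visit come after it. Later attendance can therefore respond to the infant's own growth in one arm and not in the other. Adjustment for baseline covariates cannot remove that.

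At stake is the interpretation of a secondary result. In a trial that describes itself as explanatory, an effect among completers may carry weight, and this comparison can look positive when the intervention does nothing.

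**Working it through.** **Plan's own figure.** Three sessions plus two calls make 5 contacts, and 4/5 = 80 %. The stated threshold is reproduced.

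**Inputs from the Sample size calculation section.** SD 0.87 SDS; target difference 0.20 SDS (lower end of 0.20 to 0.21); 290 per group (upper end of 250 to 290).

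**Assumed inputs.** The document gives neither a completion rate *c* nor a prognostic gap *g* between completers and non-completers. I take *c* from 60 to 90 % and *g* from 0.1 to 0.3 SDS, with completers gaining less weight in any case. If they gained more, the sign would reverse.

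**1. Intervention completers against all controls.** With no treatment effect, completers have mean m_c. Controls mix both types, with mean c·m_c + (1 − c)·m_n. Bias = (1 − c)·(m_c − m_n), of size (1 − c)·g.

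| c | g = 0.1 | g = 0.2 | g = 0.3 |
|---|---|---|---|
| 90 % | 0.01 | 0.02 | 0.03 |
| 80 % | 0.02 | 0.04 | 0.06 |
| 70 % | 0.03 | 0.06 | 0.09 |
| 60 % | 0.04 | 0.08 | 0.12 |

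At c = 75 % and g = 0.2: 0.25 × 0.2 = 0.05 SDS, a quarter of 0.20.

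**2. False-positive rate with no true effect.** SE = 0.87·√(1/(290c) + 1/290). At c = 80 %, g = 0.2: SE = 0.077 and shift = 0.04/0.077 = 0.52, so a nominal 5 % test rejects about 8 % of the time. The rate is about 10 % at 75 % and 0.2, 20 % at 70 % and 0.3, and 5 % at 90 % and 0.1.

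**3. Same rule in both arms.** In 4,000 simulated trials (290 per arm, true completer effect 0.20, g = 0.2, c = 80 %), completers against all controls gave 0.24. Completers against control completers gave 0.20, because attendance was given the same determinants in each arm.

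**4. Complier-average estimate.** CACE = intention-to-treat difference / c. For a difference of 0.20, SE = 0.87·√(2/290) = 0.072 and z = 2.77. At c = 80 %, CACE = 0.20/0.80 = 0.25, SE = 0.072/0.80 = 0.09, and z is again 2.77. It rescales the intention-to-treat result and cannot make a null one significant.

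**5. Its assumption.** If non-completers receive a fraction *f* of the full effect D, the intention-to-treat difference is D·(c + (1 − c)·f). Then CACE/D = 1 + (1 − c)·f/c. With f = 0.5 the overstatement is 6 % at c = 90 %, 13 % at 80 % (0.2 × 0.5/0.8 = 0.125), 21 % at 70 % and 33 % at 60 %. In the simulation at 80 %, CACE averaged 0.20 with f = 0 and 0.23 with f = 0.5.

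**6. Entry age.** Three months is 3 × 365.25/12/7 = 13.0 weeks, so only entry in about weeks 13 to 14 falls after the first call window. If that call were dropped, 4 of 5 would become 4 of 4. At an assumed 90 % attendance per contact, the chance of qualifying is 0.9⁴ = 0.66 instead of 5 × 0.9⁴ × 0.1 + 0.9⁵ = 0.92.

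**The case against.** The strongest reply is that nothing here is contradictory. Intention-to-treat is the main analysis, per protocol is labelled secondary, and its threshold is fixed in advance. Whether the rule covers controls is a detail that an analysis plan may settle. Controls have the same number of contacts, so the rule can be applied to them, and then the simulated bias vanishes. Covariate adjustment may reduce the bias further, and both its size and its sign rest on assumed inputs.

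Much of this stands. The primary conclusion is not at risk, and the figures illustrate the problem without predicting its size. But the wording that is printed ties the set to completing a programme that one arm receives. The both-arms result also needs attendance to have the same determinants in each arm, which intervention-only growth feedback at 4 months puts in doubt.

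Two stronger readings are tempting, and the document supports neither.

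- **A reader might infer that a complier analysis answers the same question without bias and should replace the per-protocol one.** It exchanges the selection problem for the assumption that fewer than four contacts have no effect. The first session already delivers the leaflet, recommendations and feeding plan, so that is doubtful. At 80 % attendance and half effect it gives 0.23 for a true 0.20, close to the 0.24 from completers against all controls. It also assumes that controls do not receive the intervention, although the same four nurses serve both arms. With about 15 % loss expected, the analysed infants are those with a 12-month weight, not all who were randomised.
- **A reader might infer that the 4/5 rule systematically disadvantages late entrants.** No text says that the early call is dropped for them. Entry age precedes randomisation and is expected to balance, so on its own it would not bias a rule applied to both arms.

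**Conclusion.** The concern holds in a limited form. As worded, the secondary per-protocol comparison is open to selection bias: 0.04 to 0.05 SDS against a target of 0.20 if completion is 75 to 80 % and completers differ prognostically by 0.2 SDS, and 0.01 to 0.12 SDS over the wider assumed range. These figures apply to completers against all controls, before covariate adjustment. The intention-to-treat conclusion is untouched. A complier-average estimate is worth having alongside it because it compares the groups as randomised and, when the intervention has no effect, keeps the intention-to-treat false-positive rate. It is not unbiased when partial attendance works. Entry age is a minor matter of counting, confined to about the last week of the entry window and only if the early call is dropped rather than moved. This is an improvement to a secondary analysis, not a serious defect.

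**What to change.** 1. Keep intention-to-treat as the main analysis.
2. If the per-protocol analysis is kept, state that the 4/5 attendance rule applies to both arms, and label the result a non-randomised comparison. Add one line on how contacts are counted for babies who enter after the first call window.
3. Add a complier-average causal effect: two-stage least squares, allocation as instrument for attendance at four or more contacts, the covariates of the primary model, and all randomised infants with a 12-month weight.
4. State its assumption that fewer than four contacts have no effect, say why that is doubtful here, and report a sensitivity analysis in which non-completers receive a fraction of the effect (for example one quarter, one half and three quarters).

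**Cost.** A short extra analysis on attendance and weight data that the trial already needs for its planned analyses. The price is a wider interval than intention-to-treat (SE 0.09 against 0.07 at 80 % attendance) and an assumption that must be argued openly. It adds no power.

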#### Growth

Weight, length and BMI will be converted to SDS adjusted for age and sex using the British 1990 growth reference and the WHO 2006 growth standard at different time points (birth, baseline, six and 12 months). Babies in the intervention and control groups will be compared for change in weight, length and BMI SDS from birth and baseline to 6 and 12 months. Percentage of babies crossing the 1 percentile band (0.67 SDS) in the two groups will be compared. Their abdominal circumference, sub-cutaneous and intra-abdominal fat (skin-fold thickness and ultrasound measurements) will also be compared at 1 year.

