### Sample size calculation

The primary outcome is conditional infant weight gain from birth to 12 months of age (conditional on birth weight). Birth weight and weight at 6 and 12 months will be converted to standard deviation scores (SDS) adjusted for age and sex using the WHO 2006 growth standard. SDS refers to the number of standard deviations the measurement lies above (positive value) or below (negative value) the 50^th^ percentile (median value 0). Conditional weight gain is calculated as the change in weight SDS between birth to age 12 months, adjusted for birth weight SDS.

In the Avon Longitudinal Study of Parents and Children (ALSPAC), among 518 formula and mixed-fed infants, mean ± SD for conditional weight gain was 0.65 ± 0.87, and for energy intake at 4 months was 2768 ± 479 kJ/day. Based on those data, we estimated that our target 15 % (420 kJ/day) reduction in energy intake would lead to a (mean ± SE) 0.16 ± 0.04 lower gain in weight SDS between 0 to 8 months [37]. We have powered the study on a more conservative estimate of a 10 % to 11 % achieved reduction in energy intake, which corresponds to a difference in weight SDS of 0.11 to 0.12. However, the estimated effect size should be corrected for regression dilution because energy intake in ALSPAC was estimated from unweighed 1-day diet diaries. Lanigan et al. reported the within- (778 kJ) and between-infant (824 kJ) SD during the 5-day diet diaries in the 6- to 24-month-old infants, and this gives a regression dilution correction factor of 1.89 [38]. With a 10 % to 11 % lower calorie intake in the intervention group, we can expect a 0.20 to 0.21 SDS (0.11 to 0.12*1.89) difference between the two groups.

Sample sizes of 250 to 290 infants in each group will provide 80 % power at the two sided 5 % level to detect a 0.20 to 0.21 SDS difference in weight gain between the intervention and the control group. Allowing for around 15 % loss to follow-up, we aim to recruit 300 to 350 infants to each group.

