#### Parents’ anthropometry

A useful halo-effect of our intervention would be if due to increased awareness, parents lost weight. At 12 months, we will compare parents’ BMI between intervention and control groups, adjusted for baseline measures.

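### Changes in length and BMI SDS, and in weight SDS from baseline, are not stated to be adjusted for the same measure's starting SDS, unlike the primary outcome, so some precision is lost and chance starting imbalance carries over

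*Protocol article*

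**What the plan says.** All the relevant text is in the protocol article.

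- **Primary outcome** (Sample size calculation): "Conditional weight gain is calculated as the change in weight SDS between birth to age 12 months, adjusted for birth weight SDS". Weight gain is conditioned on its own starting value.
- **Secondary growth outcomes** (Growth): babies in the two arms will be "compared for change in weight, length and BMI SDS from birth and baseline to 6 and 12 months". Conditioning on the starting value is not mentioned here.
- **General covariate rule** (Data analysis, ahead of the outcome subsections): "Comparisons will adjust for age, sex, birth weight, age when formula-milk was started, and other potential confounding variables". Birth weight is the only measure of infant size that is named, and the list is open at the end.
- **Parents' BMI** (Parents' anthropometry): "we will compare parents’ BMI between intervention and control groups, adjusted for baseline measures". Own-baseline adjustment is stated.

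The starting values are already collected. Table 1 has supine length and weight measured at baseline in both arms, and its first footnote lists birth weight and birth length among the baseline questionnaire items.

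**The concern.** On the named covariates, weight change from birth is conditioned on its own start, because birth weight is in the model. Three kinds of comparison are not: length SDS change, BMI SDS change, and weight SDS change from baseline.

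A change score without its own start as covariate fixes the slope of the final value on the starting value at 1. Where the true slope, given birth weight, is below 1, two things follow. First, variation in the starting value that does not persist stays in the outcome and widens the confidence interval. Second, if the arms differ by chance in starting length or BMI beyond what birth weight explains, part of that difference appears as an arm difference in change.

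Length and BMI SDS help a reader judge whether slower weight gain goes with less weight for length or with slower linear growth. A wider interval makes a null result on either harder to interpret. The remedy uses data in hand, and the article already applies it elsewhere.

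**Working it through.** **Inputs.** The article gives no SD, correlation, effect or sample size for length or BMI SDS, so there is no figure of its own to reproduce on this point. Its SD ("mean ± SD for conditional weight gain was 0.65 ± 0.87") and its 250 to 290 infants per group refer to weight gain. I therefore assume unit-variance SDS for the starting value S, birth weight B and the 12-month value Y, with:

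- r = corr(S, Y): 0.2 to 0.5, with 0.6 as a sensitivity value
- b = corr(S, B): 0.5 to 0.7
- y = corr(Y, B): 0.2 to 0.3

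**Step 1: the primary outcome is not affected.** With the starting value in the model, change and final value give the same arm estimate. In a simulated data set of 540 infants both gave −0.109. Weight change from birth, adjusted for birth weight SDS, is therefore already the efficient analysis.

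**Step 2: residual variances, birth weight adjusted for in both models.**

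- Change without own start: V1 = 2 − 2r − (y − b)²
- Own start added: V2 = 1 − (r² + y² − 2rby)/(1 − b²)
- Relative efficiency = V2/V1; excess standard error = √(V1/V2) − 1

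Example with r = 0.3, b = 0.5, y = 0.3:

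- V1 = 2 − 0.6 − 0.04 = 1.36
- V2 = 1 − (0.09 + 0.09 − 0.09)/0.75 = 0.88
- Relative efficiency 0.65; standard error 24 % larger

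Extremes of the assumed range:

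| r | b | y | V1 | V2 | V2/V1 | Excess SE |
|---|---|---|---|---|---|---|
| 0.2 | 0.5 | 0.3 | 1.56 | 0.907 | 0.58 | 31 % |
| 0.5 | 0.7 | 0.2 | 0.75 | 0.706 | 0.94 | 3 % |
| 0.6 | 0.5 | 0.3 | 0.76 | 0.640 | 0.84 | 9 % |
| 0.6 | 0.7 | 0.2 | 0.55 | 0.545 | 0.99 | 0.4 % |

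**Step 3: how much birth weight already recovers.** With no birth weight in either model the ratio is (1 + r)/2. Excess standard errors, with y running from 0.2 to 0.3:

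| r | No birth weight | b = 0.5 | b = 0.7 |
|---|---|---|---|
| 0.3 | 24 % | 20 to 24 % | 12 to 18 % |
| 0.5 | 15.5 % | 10 to 13 % | 3 to 6 % |

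The recovery is substantial when birth weight tracks the starting value closely. It is slight when the correlation is 0.5 and r is low.

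**Step 4: chance imbalance.** Take 270 analysed infants per arm, the middle of the article's 250 to 290. The standard error of the arm difference in a starting SDS is √(2/270) = 0.086, or 0.086 × √(1 − b²) beyond birth weight. The slope of Y on S given B is β = (r − by)/(1 − b²). A one-standard-error imbalance shifts the arm difference in change by (1 − β) × 0.086 × √(1 − b²).

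- In the example β = (0.3 − 0.15)/0.75 = 0.2, and the shift is 0.8 × 0.086 × 0.866 = 0.060 SDS.
- Over r = 0.2 to 0.5 the shift runs from 0.018 (r = 0.5, b = 0.7, y = 0.2) to 0.070 SDS (r = 0.2, b = 0.5, y = 0.3).

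**The case against.** The best defence is textual. The article uses the bare word change loosely: the abstract and Data analysis describe the primary outcome that way too, although it is defined as conditional. The covariate list is open-ended and could admit the starting value. A condensed article also commonly leaves the covariates of each secondary model to an analysis plan, and one may exist.

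Much of this stands. A reader might infer that length and BMI will be analysed as raw, unadjusted change. The text does not support that, since Data analysis adjusts comparisons for birth weight and other covariates. Nor does it support a claim of systematic bias: under randomisation both estimators are unbiased, and only precision and chance imbalance are at issue.

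Three further inferences should not be drawn:

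- Recording length to 0.5 cm does not drive the loss. Rounding adds an error SD of only 0.5/√12 = 0.14 cm.
- Power for length or BMI cannot be read from the 0.20 to 0.21 SDS difference. That is the weight target, and the article sets none for the other measures.
- Nothing in the article requires the baseline version to lead over the birth version. That is a matter of preference.

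What the defence does not remove is the contrast within the article. Own-start adjustment is written out for the primary outcome and for parents' BMI, but for the infant growth outcomes only birth weight is named. An open list permits the starting value without committing to it, and adding it after seeing an imbalance would be a post hoc choice.

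**Conclusion.** The point holds as a moderate, inexpensive improvement to secondary outcomes. On the covariates named, change in length SDS and BMI SDS, and weight SDS change from baseline, are not conditioned on their own starting value. Under the assumed correlations the relative efficiency is about 0.58 to 0.94, and a one-standard-error chance imbalance moves the arm difference by about 0.02 to 0.07 SDS.

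The size rests wholly on correlations that the article does not give. It shrinks as the start-to-end correlation rises: at 0.6 the relative efficiency is 0.84 to 0.99. Shorter intervals, such as baseline to 6 months, may have higher correlations and so a smaller gain. The primary outcome is unaffected.

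**What to change.** Add one sentence under Growth: each change in weight, length and BMI SDS is adjusted for the same measure's SDS at the start of its interval (birth or baseline, as applicable), in addition to the covariates named under Data analysis. For weight change from birth this only restates the primary definition.

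The cost is one covariate, hence one degree of freedom, per model. No new data are needed, because birth and baseline measures are already collected. If an analysis plan exists, the same sentence should stand there.
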